### Study withdrawal

Given that the primary and secondary outcomes require the measurement of cardiac autonomic tone with a Holter monitor, follow up for these outcomes can only occur if the subject is alive and accessible for monitoring. Therefore, subjects will be censored and withdrawn from follow-up under the following circumstances; subject or primary nephrologist request, transfer to peritoneal dialysis, kidney transplantation, transfer of subject to a non-study hemodialysis unit, hospitalization, or death. Upon withdrawal from the study, any data collected up to that time will be utilized in a last observation carried forward (LOCF) approach.

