## Background

More than 40,000 Canadians live with end-stage kidney disease (ESKD)—roughly 1 out of every 1,000 people, a number that has tripled over 20 years – and require life-sustaining dialysis or transplantation [1]. Patients with ESKD have a 20% annual mortality rate and an age-specific cardiovascular death rate that is 10-100x higher than the general population [2]. Sudden cardiac death (SCD) accounts for more than a quarter of deaths in the hemodialysis population, making it the leading cause of death [2]. However, as is repeatedly reflected by negative trials evaluating the effects of treatment of traditional cardiovascular disease risk factors in patients with ESKD [3-6], these deaths are not associated with typical coronary artery disease, suggesting alternative mechanisms for SCD in ESKD. As such, the pathophysiology of SCD in the ESKD population is complex and believed to require the interaction between a transient event (i.e. intermittent hemodialysis) and underlying substrate. This process induces electrical instability and ventricular arrhythmias followed by hemodynamic collapse. Two factors specific to ESKD patients that have emerged as potential contributors to this SCD-susceptible state are altered mineral metabolism, including vitamin D deficiency, and impaired cardiac autonomic tone [7-10].

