### Identification of eligible subjects

Eligible subjects are stable, thrice weekly hemodialysis outpatients within the Southern Alberta Renal Program in Calgary, Alberta. Inclusion and exclusion criteria are outlined in Table 1. All patients in the Southern Alberta Renal Program hemodialysis units will be reviewed. Individuals who meet inclusion criteria will be identified by nephrologists or study investigators. After clearance from the individual’s primary nephrologist, the name will be forwarded to the study coordinators and recorded in recruitment logs. Informed written consent will be obtained from the participant, power of attorney or legal substitute decision-maker. Once eligibility is confirmed by reviewing the chart or from participant interview, baseline clinical (i.e. ESKD etiology, comorbidities, cardiovascular history, dialysis prescription and adequacy details), demographic and medication data will be obtained. Subjects will be randomized 1:1 to one of the two treatment sequences.

**Table 1 T1:** VITAH trial inclusion and exclusion criteria

**Inclusion criteria**	**Exclusion criteria**
• Age ≥ 18 years	• Any major cardiovascular event within the last 6 months prior to enrolment (this includes, but is not limited to, new onset arrhythmia, hospitalization for a cardiovascular complication)
• Thrice weekly hemodialysis outpatient within the Southern Alberta Renal Program	
• Physician consent to participate	• Refusal to cease vitamin D therapy for four (4) weeks prior to initiation of the study
• Ability and agreement to cease any prior vitamin D medication for four (4) weeks prior to initiation of the study	• Palliative status or metastatic malignancy
• Ability to comprehend study protocol and provide oral and written consent in English (native language or translated)	• Known or anticipated upcoming change in dialysis modality including transfer to peritoneal dialysis, kidney transplant, or change in current hemodialysis schedule/duration

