### Sample size calculation

While we are not aware of any studies examining the use of vitamin D on the primary outcome of this study, previous work by Kontopoulous et al. [47] has demonstrated that post-myocardial infarction (MI) patients (n = 25) randomized to receive 5–10 mg of quinapril (angiotensin converting enzyme inhibitor) per day for 35 days immediately following an MI displayed a 46% reduction in LF:HF from baseline to 6 weeks (mean ± SE: 10 ± 0.7; 5 ± 0.5), while those randomized (n = 25) to receive 50–100 mg of metoprolol per day for 35 days following an MI displayed a similar 36% reduction in LF:HF from baseline to 6 weeks (mean ± SE: 9 ± 0.6; 6 ± 0.4). As such, given that 1) vitamin D deficiency is the norm in hemodialysis patients, 2) vitamin D downregulates the renin-angiotensin system [24,25,35], and 3) increased RAS activity is associated with alterations in cardiac autonomic tone [35-37], we feel there is sufficient justification for the sample size calculation herein**.** Based on these observations, we estimate the standard deviation of the pooled difference in LF:HF from both treatment sequences as 4.53. Using a 2 × 2 crossover design (2 sequences or treatment orderings and 2 time periods or occasions) and anticipating a 20% or larger reduction in LF:HF observed after 6 weeks of treatment with combined vitamin D vs. the reduction observed after 6 weeks of treatment with alfacalcidiol alone, we estimate that 54 subjects will be required (α = 0.05, β = 0.9). In anticipation of a 10% dropout rate, approximately 60 subjects in total will be recruited.

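### Any hospitalization ends outcome follow-up for good, and the 10% dropout allowance, about equal to the deaths implied by the protocol's own mortality figure, leaves almost no room for it

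*Protocol article*

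**What the plan says.** The Study withdrawal section reasons that the primary and secondary outcomes can be followed only in a subject who is alive and can be reached for Holter monitoring. From this it derives a list of events on which subjects are censored and withdrawn: request by the subject or nephrologist, transfer to peritoneal dialysis, transplantation, and "transfer of subject to a non-study hemodialysis unit, hospitalization, or death". Hospitalization carries no qualifier of cause or duration, and no re-entry is described. Data collected before withdrawal are then used by last observation carried forward (LOCF).

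The Sample size calculation requires 54 subjects and adds one allowance for all losses: "In anticipation of a 10% dropout rate, approximately 60 subjects in total will be recruited". It gives no basis for the 10%.

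The Background states: "Patients with ESKD have a 20% annual mortality rate". No hospitalization rate appears anywhere in the article.

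**The concern.** Two things do not fit together.

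**The rule and its reason.** Death makes the outcome unobservable, and transfer to a non-study unit plausibly does so in practice. An admission makes the subject unreachable only for a time. The Primary outcome section needs Holters at weeks 0, 6, 18 and 24. Under the rule as written, an admission at any point, including the 12-week washout when no study treatment is scheduled, removes every later recording and with it the within-subject comparison. The Background ties impaired autonomic tone to cardiovascular death, so subjects lost through admission plausibly differ from the rest on the very quantity being measured.

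**The rule and the allowance.** If every admission is a permanent loss, the dropout allowance must cover admissions as well as deaths, transplants, modality changes, transfers and requests. An allowance that deaths alone could nearly exhaust does not do that. Power and the credibility of the paired analysis are at stake.

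**Working it through.** **Step 1: reproduce the plan's figure.** Inputs from the Sample size calculation:
- "α = 0.05, β = 0.9", with 0.9 read as power and α as two-sided;
- SD of the within-subject difference 4.53 ("we estimate the standard deviation of the pooled difference in LF:HF from both treatment sequences as 4.53");
- a 20% effect ("anticipating a 20% or larger reduction in LF:HF observed after 6 weeks of treatment with combined vitamin D"). Applied to the cited baseline of 10 ("mean ± SE: 10 ± 0.7; 5 ± 0.5"), this gives a difference of 2.0. The base of 10 is inferred, but it is the one that reproduces the result.

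n = ((1.960 + 1.282) × 4.53 / 2.0)² = 53.9, rounded up to 54. Then 54 / 0.90 = 60. Both figures reproduce under the normal approximation. The allowance is 60 − 54 = 6 subjects.

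**Step 2: deaths over 24 weeks at 20% a year.**
- Compounding: 1 − 0.8^(24/52) = 9.8%, or 5.9 of 60.
- Linear: 0.20 × 24/52 = 9.2%, or 5.5 of 60.
- 0.20 as a hazard: 1 − exp(−0.20 × 24/52) = 8.8%, or 5.3 of 60.

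Deaths would therefore use 88% to 98% of the allowance and leave 0.1 to 0.7 of a subject for all other reasons. As rates, a 10% loss in 24 weeks equals −ln(0.9) × 52/24 = 0.228 per patient-year from all causes; 20% annual mortality alone equals −ln(0.8) = 0.223.

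Deaths alone still leave 60 × 0.8^(24/52) = 54.1 expected completers, with a binomial probability of 0.63 of at least 54.

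**Step 3: add non-death withdrawals.** The rate h per patient-year, covering hospitalization and all other non-death reasons together, is an assumption.
- Completers = 60 × (1 − m)^(24/52) × exp(−h × 24/52), where m is annual mortality.
- Power = Φ(2.0 × √completers / 4.53 − 1.960), the approximation that gives 54.

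| h per patient-year | Completers, m = 20% | Power | Completers, m = 10% (assumed) | Power |
|---|---|---|---|---|
| 0 | 54.1 | 0.901 | 57.2 | 0.916 |
| 0.10 | 51.7 | 0.888 | 54.6 | 0.903 |
| 0.25 | 48.2 | 0.866 | 50.9 | 0.883 |
| 0.50 | 43.0 | 0.825 | 45.4 | 0.845 |
| 1.0 | 34.1 | 0.732 | 36.0 | 0.755 |

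At 10% annual mortality, deaths over 24 weeks number 60 × (1 − 0.9^(24/52)) = 2.8, about half the allowance.

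**Step 4: what LOCF does.** Carrying the last Holter forward sets the change to zero in any block whose end-of-block recording is missing.
- A subject lost in the first block contributes zero to the paired contrast.
- A subject lost after week 6 contributes the first-block change against zero. Write I and C for the mean changes on intensive and conventional therapy. If such losses are equal in the two sequences, the average contribution is ½(I − 0) + ½(0 − C) = ½(I − C), half the treatment difference.

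The nominal N is kept, but the contrast is diluted.

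**The case against.** **A shortfall below 54 is not shown.** A reader might infer that the trial cannot reach 54 completers. The document does not support that: deaths at 20% a year leave 54.1 expected, and a shortfall needs a non-death withdrawal rate that the article does not give. This stands.

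**The 20% describes another population.** It is quoted for ESKD patients in general. The trial enrols stable outpatients and excludes a major cardiovascular event within 6 months, palliative status, metastatic malignancy and any anticipated change of modality, transplant or schedule. Mortality and some other losses may well be lower. This also stands, and it is why the table carries 10% as an alternative.

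**Admissions and deaths overlap.** Many deaths may follow an admission, so treating the two as independent can count some losses twice. The completer counts are therefore on the low side for any given admission rate.

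**LOCF keeps subjects in the analysis.** The analysed N need not fall to the completer count, so the powers above describe an analysis of completers. But LOCF supplies no second-block response, so it does not rescue the contrast.

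**Sequence imbalance.** A reader might infer that the rule unbalances the two sequences. Nothing supports this: both sequences receive both regimens ("Subjects will be randomized 1:1 to one of the two treatment sequences"), and no differential admission is suggested.

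**An article may leave visit windows and re-entry to the full protocol.** That is fair for windows. Here, however, the article states an explicit rule and derives it from a reason that does not cover hospitalization.

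**Conclusion.** The point holds in two parts and should be corrected.

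First, as written, the rule permanently ends outcome follow-up on any hospitalization, for a reason that lapses on discharge to the same unit. It loses measurable subjects in a prognosis-linked way, and LOCF dilutes the contrast instead of recovering it. This part needs no assumed rate.

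Second, the allowance of 6 subjects is about equal to the 5.3 to 5.9 deaths implied by the Background's mortality figure, so almost nothing is budgeted for the other listed reasons. At half that mortality, about half the allowance remains, which covers non-death withdrawals of about 0.10 per patient-year but not 0.25.

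The power loss depends on an unknown rate. It is small at 0.10 per patient-year (0.888 against the planned 0.90 at 20% mortality) and material at 0.50 to 1.0 (0.825 to 0.732). These figures assume a difference of 2.0, an SD of 4.53, constant hazards, and independence of death and other withdrawals.

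**What to change.** - **Study withdrawal:** remove hospitalization as an automatic reason to end outcome follow-up. After discharge, take the remaining scheduled Holters at the study unit and flag any displaced by an admission.
- **On-treatment status:** do not count a Holter recorded after the block's treatment has ended as an on-treatment endpoint. Blocks last 6 weeks, and the Study interventions section gives half-lives of about 4 hours and 19–48 hours, so a postponed week-6 or week-24 recording could be off treatment. Add a sensitivity analysis without flagged recordings.
- **Study drug:** leave these decisions as the Subject follow-up procedures section has them. The change concerns outcome measurement only.
- **Sample size calculation:** reconcile the 10% with the Background's mortality figure and the withdrawal list. State the mortality and hospitalization rates assumed for this sample, and restate expected completers and power.

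The cost is rewording, some rescheduling, and noisier recordings shortly after an admission.

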### Study design and setting

The VITAH Trial is a 2x2 cross-over, randomized-controlled trial with blinding of subjects, investigators, health care providers, as well as all study coordinators and data analysts. Hemodialysis outpatients from the Southern Alberta Renal Program will be randomized to one of two treatment sequence arms; 6 weeks of intensive vitamin D therapy (0.25 mcg alfacalcidiol at each dialysis session plus 50,000 IU of ergocalciferol once per week and placebo the remaining two weekly dialysis days), followed by a 12 week washout, and 6 weeks of conventional vitamin D therapy (0.25 mcg alfacalcidiol plus placebo at each dialysis session), or vice versa. Twenty-four hour Holter ECG monitors are applied within the first hour of the first weekly dialysis run at baseline and every 6 weeks throughout the entire 24-week duration of the trial (Figure 1). The study protocol will not impact on uremia clearance given that the dialysis prescription will remain constant. Subject recruitment began in January 2013 and will continue until 2016.

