### Study interventions

The intervention is the vitamin D therapy sequence, including 6 weeks of intensive therapy and 6 week of conventional vitamin D therapy, or vice versa (Figure 1). Given that the current clinical standard of care is use of activated vitamin D (one of the top drug classes prescribed as recently outlined in the United States Renal Data System [44]) in the ESKD population, a placebo arm is not included. Upon recruitment, participants who are prescribed any form of vitamin D (either nutritional or active) at that time will cease to take the medication for 4 weeks, a valid washout period employed by the PRIMO trial, a randomized controlled trial examining the effects of activated vitamin D on cardiac structure in subjects with non-dialysis dependent kidney disease [45]. Participants who are not on any form of vitamin D at the time of enrolment will be randomized to one of the two treatment sequences immediately. All participants will be randomized to Treatment Sequence 1 or Treatment Sequence 2, such that each participant will ingest both vitamin D therapy regimens in a randomized, blinded, placebo-controlled crossover design and thus act as his/her own control. A 12 week washout period was chosen between each 6 week vitamin D treatment block to ensure that there are no carryover effects from either study period as the t_1/2_ for alfacalcidiol is approximately 4 hours, and the t_1/2_ for ergocalciferol is 19–48 hours [22,23,46].

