### Primary outcome

The primary outcome of the study is sympathovagal balance (LF:HF), interpreted as the overall balance on stimulatory and inhibitory cardiac autonomic control, from baseline to the final study day within each 6 week treatment block (0 and 6 weeks, 18 and 24 weeks). Comparison of measured sympathovagal balance throughout each of the vitamin D supplementation treatment blocks as well as the 12-week washout period will allow for statistical interpretation of whether presence or absence of oral vitamin D therapy alters cardiac autonomic function within this population. An improvement in sympathovagal balance can be interpreted by a downward shift in LF:HF, in which a smaller value indicates greater contribution of cardioprotective vagal activity (Table 2).

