### Statistical analysis

The primary analysis will test associations between intensive and conventional vitamin D therapies and observed fluctuations in LF:HF from baseline to 6 weeks later within each treatment block utilizing a non-parametric paired t-test. To further determine the relationships between cardiac autonomic tone and specific vitamin D therapy regimens, we will use a repeated measurements analysis of variance model to account for the cross-over design of the study utilizing Greenhouse-Geisser correction values to account for multiple comparisons. Treatment, treatment period, and treatment sequence will be analyzed as fixed effects within the model, as well as additional effect modifiers (gender, vitamin D, calcium, phosphate, parathyroid hormone). Additional analyses will include a subgroup analysis for those subjects with diabetes mellitus as diabetes has been shown to alter parameters of cardiac autonomic tone and vitamin D metabolism [9,21].

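### Carrying the last observation forward scores an unreached or unfinished treatment block as zero change and so distorts the paired primary contrast, modestly at the planned dropout

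*Protocol article*

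**What the plan says.** Four statements in the Protocol article bear on this point.

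- **Study withdrawal.** "subjects will be censored and withdrawn from follow-up under the following circumstances"; the list includes personal or physician request, change of modality, transplantation, transfer to a non-study unit, hospitalization and death. For these subjects "any data collected up to that time will be utilized in a last observation carried forward (LOCF) approach". No restriction to a block and no alternative method is given.
- **Primary outcome.** LF:HF is assessed "from baseline to the final study day within each 6 week treatment block (0 and 6 weeks, 18 and 24 weeks", so each subject has two changes, one per treatment.
- **Statistical analysis.** The two treatments are compared on the change "from baseline to 6 weeks later within each treatment block utilizing a non-parametric paired t-test".
- **Study design and setting.** Holter recordings are made "at baseline and every 6 weeks throughout the entire 24-week duration of the trial", that is at weeks 0, 6, 12, 18 and 24.

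The sample size section requires 54 subjects and recruits about 60 to allow for 10% dropout.

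**The concern.** Carrying a value forward may be tolerable for a single end-of-study measurement. Here the outcome is a change between two visits, taken twice. If a subject leaves before the second visit of a block, the carried value fills the missing end of that block, and both ends if the block was never started. The change is then 0 by construction.

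The paired analysis subtracts one block change from the other. When the second block is filled in this way, the subject's contrast is simply the first-block change, positive or negative according to which treatment came first. That is not the treatment difference the trial sets out to estimate. These invented contrasts also enter the standard error as if they had been observed. A crossover normally cancels whatever change is common to both treatments; for these subjects it no longer does, so the estimate depends on which sequence loses more of them.

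**Working it through.** **1. The plan's own figure.** Inputs from the sample size section: "we estimate the standard deviation of the pooled difference in LF:HF from both treatment sequences as 4.53"; 10% dropout; alpha 0.05; power 0.90 (printed as β = 0.9). Two-sided testing is assumed. The effect is given only as a relative figure ("anticipating a 20% or larger reduction in LF:HF observed after 6 weeks of treatment with combined vitamin D"). Taking 20% of the cited baseline of 10 gives a difference Δ of 2.0, which is an assumption.

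n = (SD × (z0.975 + z0.90) / Δ)² = (4.53 × (1.960 + 1.282) / 2.0)² ≈ 53.9, so 54. Then 54 / 0.90 = 60. Both stated figures reproduce.

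**2. What a withdrawn subject contributes.** Let cI and cC be the mean changes on intensive and conventional therapy, with Δ = cI − cC. For illustration take cI = −5 and cC = −3, the changes in the two arms of the cited post-infarction study (10 to 5 and 9 to 6), so Δ = −2.

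| Withdrawal | Contrast under the literal rule | Illustration |
|---|---|---|
| Before week 6 | 0 − 0 | 0 |
| After week 6, intensive first | cI − 0 | −5 |
| After week 6, conventional first | 0 − cC | +3 |
| After week 6, sequences balanced | (cI − cC)/2 | −1 |

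The second-block change is 0 whether the carried value comes from week 6, 12 or 18.

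**3. Expected estimate when dropout is balanced and unrelated to outcome.** With dropout fraction d, the mean is (1 − d)Δ + d × (contrast of those lost).

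- d = 0.10, all before week 6: 0.9 × (−2) + 0.1 × 0 = −1.80, a 10% dilution.
- d = 0.10, all after week 6: 0.9 × (−2) + 0.1 × (−1) = −1.90, a 5% dilution.
- d = 0.10, half of each: −1.85.
- d = 0.20 (an assumption, twice the plan's figure): −1.60 to −1.80.

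The relative dilution is d for early losses and d/2 for late ones, whatever cI and cC are. Simulation with 60 subjects and 6 lost gave −1.82, −1.85 and −1.90, against about −2.00 for complete pairs.

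**4. When losses differ by sequence.** Suppose all six losses occur after block 1.

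- All intensive first: 0.9 × (−2) + 0.1 × (−5) = −2.3.
- All conventional first: 0.9 × (−2) + 0.1 × 3 = −1.5.
- With smaller assumed changes, −3 and −1: −2.1 and −1.7.
- With −2 and 0: −2.0 and −1.8.

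With no true difference (both changes −3), 10% lost from intensive first and 30% from conventional first, the spurious mean is ½ × 0.10 × (−3) + ½ × 0.30 × 3 = +0.3. The simulated type I error is about 7%, against about 5% for complete pairs.

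**5. Power under balanced dropout.** Simulation used 30 per sequence, changes −5 and −3, SD 3 per measurement, within-subject correlation 0.35, losses during the washout and a paired t-test:

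| Dropout | Carried forward | Complete pairs |
|---|---|---|
| 10% | 0.845 | 0.849 |
| 20% | 0.794 | 0.800 |
| 30% | 0.737 | 0.731 |

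The two columns are practically the same.

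**The case against.** **The rule may be meant only within a block.** The article does not say that values pass through the washout ("A 12 week washout period was chosen between each 6 week vitamin D treatment block") into a block never started. Raising 54 to 60 also fits an analysis of completers better than one that fills in all 60. This stands in part: carrying across the washout is the literal reading but not the only one. Under the narrower reading, a subject who stops between blocks has no pair and drops out of the paired test. A subject lost between weeks 18 and 24 still gets an invented 0, and so again contributes only the first-block change. One lost between weeks 0 and 6 gets an invented 0 for the first block. The rule needs rewording on either reading.

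**The bias is small at the planned dropout.** This stands. With a standard error of 4.53/√60 ≈ 0.58, a shift of 0.1 to 0.2 is about 0.17 to 0.34 standard errors.

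**The −5 and −3 are borrowed.** They come from post-infarction patients on other drugs, and the protocol does not assume them for this trial. This limits the figures for unequal losses, which shrink as the changes shrink. It does not touch the 5% to 10% dilution, which does not depend on them.

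**Unequal dropout is hypothetical.** Allocation is 1:1 and blinded, and both regimens contain alfacalcidiol. Nothing in the article predicts a threefold imbalance, so step 4 shows sensitivity and is not a forecast.

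**The detail belongs in a fuller plan.** How the rule is operated may be set out there. But the article itself names the method and offers no other, so this is a stated choice and not an omission.

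**Conclusion.** The concern holds in a limited form: the rule should be changed, but it does not invalidate the trial. As written, it distorts the primary contrast. The expected dilution is 5% to 10% at 10% dropout if losses are balanced and unrelated to outcome. The shift can go in either direction, with some inflation of the type I error, if losses differ by sequence. The absolute figures rest on an assumed difference of 2.0, and those for unequal losses also on the borrowed block changes. If the named test is a signed-rank test that discards zeros, subjects lost before week 6 do not affect the p-value, but those lost later still do.

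Three stronger readings are not supported.

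- A reader might infer a loss of power, since power falls from about 0.89 with no dropout to about 0.79 at 20%. Complete pairs fall equally, so the loss comes from having fewer complete subjects and not from carrying values forward.
- A reader might infer that the rule always dilutes. That is the expectation only when losses are balanced.
- A reader might infer that the carried value always comes from the other treatment. With recordings at weeks 12 and 18 it may be a washout value or the second block's own baseline.

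**What to change.** Remove the carry-forward rule from the primary analysis. Use a likelihood-based mixed model on the observed LF:HF values or observed block changes, with treatment, period and sequence as fixed effects (the Statistical analysis section already names these) and subject as a random effect. A subject with one observed block then contributes that block and nothing is filled in.

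This model relies on dropout being explained by the observed data, and some listed withdrawal reasons, such as hospitalization and death, may not satisfy that. Report two sensitivity analyses: complete pairs, and multiple imputation with a delta adjustment.

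The cost is a sentence or two in the protocol and analysis plan and a little extra analysis work. No new data are needed.
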